## Abstract

Enteral nutrition (EN) has become the standard of care for nutritional support among critically ill patients. However, little is known about whether continuous delivery (CEN) or intermittent delivery (IEN) is preferable or the consequences of either strategy. This is particularly true for diarrhea, which is understudied but consistently shown to be associated with increased morbidity among critically ill patients. This is a multicenter, retrospective cohort study including critically ill patients greater than 18 years of age, admitted to the Intensive Care Unit in Hamilton, Canada, and prescribed EN for greater than 48 hours. Patients will be divided into IEN and CEN groups based on the nutritional strategy they received during their stay. The primary outcome will be the proportion of patients in each group with diarrhea during their ICU stay, diarrhea will be defined according to WHO criteria. Multivariate logistic regression will be performed to identify the role of covariates in the risk of developing diarrhea. Secondary outcomes will include caloric intake, incidence of ICU-acquired infections, including *Clostridioides difficile*, length of stay, and mortality. This study protocol has been approved by the Hamilton Integrated Research Ethics Board (#16453). The study findings will be disseminated at academic conferences and published in peer-reviewed journals.

## Introduction

Over the last thirty years, nutrition in the intensive care unit (ICU) has evolved from supportive therapy to an active treatment that can attenuate the harms of critical illness [1]. Early nutrition, delivered enterally, has become the standard of care for most critically ill patients and is recommended by the major organizations for clinical nutrition and critical care [1–4]. Enteral nutrition (EN) offers many physiological benefits throughout the gastrointestinal (GI) tract, including maintenance of intraepithelial junctions, mucosal lymphoid tissues, and villous height and lower infection risk by preventing bacterial translocation [5]. Furthermore, clinical studies have demonstrated a benefit with a recent meta-analysis by the European Society of Intensive Medicine (12 randomized controlled trials (RCTs), 597 patients) demonstrating a reduction in infectious morbidity when EN was delivered within 48 hours of ICU admission [3]. Another meta-analysis, including 6 RCTs and 5025 critically ill patients, showed a reduction in mortality with early EN compared to parenteral nutrition (PN) [4]. Despite this and guidelines recommending early initiation of EN, malnutrition in ICUs continues to be a problem with 56–68% of patients in Canadian ICUs being underfed relative to their calculated caloric requirements [6].

While guidelines agree on the value of early EN, there is little consensus on how feeds should be delivered [1,4]. Broadly, there are two methods for EN delivery: continuous enteral feeding (CEN), which consists of low rates of tube feeds over a 24-hour period, and bolus/intermittent enteral feeding (IEN), which consists of higher rates of tube feeds delivered over shorter time periods. The American Society of Parenteral and Enteral Nutrition (ASPEN) recommends avoidance of IEN in high-risk patients based on 2 small RCTs which showed a trend towards higher mortality with IEN (13.9% IEN vs 7.4% CEN; p = 0.18) and increased risk of ventilator association pneumonia with IEN (49.3% IEN vs 30.9% CEN, p=0.02) [1,7,8]. However, both trials were published more than 15 years ago. The European Society of Parenteral and Enteral Nutrition (ESPEN) recommends avoidance of IEN in general, citing trends towards worsening diarrhea in 5 small prospective studies [4]. In contrast, 2 meta-analyses, one including 5 RCTs (392 patients) and the other including 9 RCTs (690 patients) have shown no important difference in diarrhea, vomiting, nausea or mortality in patients fed via IEN vs CEN [9,10].

Just as the mode of EN delivery is understudied, so too are the effects of critical illness on the GI tract. Feeding intolerance, diarrhea, vomiting, and ileus are common and associated with increased mortality [11]. While challenging to define, a recent multi-center cohort study found the incidence of diarrhea was as high as 38% with various definitions [12]. Diarrhea has been consistently shown to increase length of stay and contribute to morbidity in ICU patients [11–12,14]. While EN in general has been associated with higher rates of diarrhea [13], the effect of EN strategy (IEN vs CEN) on diarrhea is still unclear. Two recent RCTs including 120 and 112 mechanically ventilated patients respectively found no significant difference in diarrhea, constipation or vomiting [15,16].

Taken together, EN has become the standard of care for most critically ill patients, but little is known about optimal EN strategy or its effect on diarrhea. This is a pragmatic retrospective cohort study that will compare patients receiving IEN and CEN by determining the differences in diarrhea incidence and nutritional exposures, such as the type and volume of EN that patients receive.

Our cohort will also capture patients receiving non-invasive positive pressure ventilation (NIPPV). NIPPV has become the standard of care for several indications and is integral for managing acute exacerbations of cardiopulmonary diseases [17]. There is a growing population of critically ill patients who remain on NIPPV for extended periods and whose optimum feeding strategy is unclear. As such, we will also describe the current nutritional strategies used for patients on NIPPV.

## Methods

### Design

We will conduct a retrospective multicentre cohort study, that evaluates the outcomes of patients with a prescription for enteral nutrition or are receiving NIPPV for >48 hours admitted to three academic ICUs in Hamilton, Ontario.

### Participants

We will include all patients 18 years of age or older admitted to the ICU for at least 24 hours who have a prescription for EN or are receiving NIPPV for greater than 48 hours. Patients who received majority NIPPV for 48 hours at any one time will also be included even if they were not prescribed EN. EPIC Hyperspace is now the Electronic Medical Record (EMR) used in hospitals in Hamilton. We will include patients admitted to the ICU since EPIC went live at each site. For St. Joseph’s Hospital Hamilton (SJHH) this is between January 1, 2018, and December 31, 2023. For the two sites at Hamilton Health Sciences (HHS), this is between June 4, 2022, and December 31, 2023. Exclusion criteria includes patients receiving only nocturnal NIPPV, patients who have had gastrointestinal surgery in the month preceding ICU admission, and patients who have confirmed or suspected luminal obstruction on admission. For the purposes of this study NIPPV will exclude high flow nasal canula (HFNC).

### Data collection

Data will be collected using the search function of EPIC Hyperspace and assistance from HHS and SJHH Information Technology (IT) services teams. The MRN numbers of patients meeting the inclusion criteria will be identified. The data will be exported directly to excel. Any missing data from IT reports will be entered via manual chart review. For each recruited patient, the following baseline characteristics will be recorded to determine factors associated with intolerance of IEN or CEN and with the development of ICU-acquired diarrhea. The baseline characteristics will include demographic data, anthropometric data, clinical data on Day 1 of ICU stay (surgical, medical vs trauma admission, diagnostic category, admitting diagnosis, ventilation status, inotrope/ vasopressor use, renal replacement therapy), admitting hospital, medical comorbidities (prior GI disease, previous luminal surgeries), nutritional assessment (caloric goals on admission will be determined using weight and registered dietician assessment), antibiotic prescription on admission and serum albumin on ICU admission. Table 1 outlines the primary and secondary outcomes as well as the data that will be recorded each day of the ICU admission up until the 30th day or ICU discharge. This includes mode of nutrition (IEN, CEN, oral, or PN), daily caloric intake, mode of ventilation (Invasive, NIPPV), presence of diarrhea, bacteremia greater than 48 hours after admission (gram-positive bacilli and coagulase-negative staph will be reviewed and omitted if team feels it is more likely contaminant), incidence of aspiration pneumonia/pneumonitis, *Clostridioides difficile* infection (CDI), presence of vomiting, ileus or abdominal distention, vasopressor/inotrope dose, average daily insulin dose and blood glucose, survival status in ICU, ICU length of stay. Survival to hospital discharge and hospital length of stay will be collected for the entire hospital stay.

**Table 1 pone.0322122.t001:** Statistical Plan.

Research Objectives	Outcome	Covariates/Subgroups	Analytical Approach
To determine the incidence of diarrhea amongst patients on IEN and CEN	WHO-defined diarrhea	N/A	Descriptive statistics (proportion of patients with diarrhea) and corresponding 95% CI
To determine risk factors associated with diarrhea during ICU admission	**Dependent Variable** WHO-defined diarrhea	Age, sex, type of nutrition (IEN/CEN), antibiotics, GI comorbidities, vasopressor/inotropes, daily caloric intake, NIPPV, surgical/trauma/medical admission	Logistic Regression
Secondary Outcomes			
**Research Objectives**	**Outcome**	**Covariates/Subgroups**	**Analytical Approach**
To determine whether IEN or CEN is better for reaching caloric requirements during ICU stay	**Dependent Variables:** Average caloric intake (percent goal determined by RD or 25 kcal/kg) at 48 hours and 7 days after initiation of CEN/IEN Proportion of patients on PN at 48 hours and 7 days after initiation of CEN/IEN	NIPPV, Age, sex, antibiotics, GI comorbidities, type of nutrition (IEN/CEN) vasopressor/inotropes, daily caloric intake, surgical/trauma/medical admission	Descriptive statistics (average caloric intake) and corresponding 95% CI Descriptive statistics (proportion of patients on PN) and corresponding 95% CI Logistic regression
To determine whether IEN or CEN is associated with ICU-acquired bloodstream infection or *Clostridium difficile* infection	Incidence of positive blood cultures drawn at least 48 hours after admission, excluding coagulase-negative staphylococcus unless suspected by ICU team to not be contaminant.	NA	The incidence of bloodstream infections will be computed as the number of new cases during ICU stay divided by the person-time at risk. Descriptive statistics (proportion of patients with ICU-acquired bloodstream infection or *C. difficile infection*) and corresponding 95% CI
To determine whether IEN or CEN is associated with differences in mortality or length of stay (ICU or hospital)	**Dependent Variables** Mortality (ICU and hospital) Length of stay (ICU and hospital)	Age, sex, type of nutrition (IEN/CEN), antibiotics, GI comorbidities, vasopressor/inotropes, daily caloric intake, NIPPV, surgical/trauma/medical admission	Descriptive statistics (mortality and length of stay) and corresponding 95% CI Logistic regression
To determine whether IEN or CEN is associated with differences in aspiration pneumonia/pneumonitis	Incidence of aspiration pneumonia/pneumonitis, determined pragmatically by ICU team	NA	The incidence of aspiration pneumonia/ pneumonitis will be computed as the number of new cases during ICU stay divided by the person-time at risk. Descriptive statistics (proportion of patients with aspiration pneumonitis/ pneumonia) and corresponding 95% CI

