For the secondary outcomes patients also be divided into those who have received NIPPV and those who have not. For the purposes of this study, NIPPV will exclude HFNC but will include bilevel positive airway pressure (BiPAP) and continuous positive airway pressure (CPAP) delivered via any interface. To evaluate the relationship between IEN, CEN and NIPPV on caloric goals, each patient’s caloric intake at 48 hours and 7 days will be divided by their 24 hour caloric target (as determined by RD assessment and by the algorithm 25 kcal/kg) (Table 1). The average of these percentages with associated 95% CI will be calculated in each group. The proportion of patients in each group receiving supplement parenteral nutrition at these time points will also be determined to help evaluate the effectiveness of each EN strategy (Table 1). Logistic regression will also be applied to evaluate the role of covariates; specifically baseline characteristics and the effect they may have on patients reaching their caloric targets (Table 1). In terms of other secondary outcomes, the incidence of hospital acquired infections, ICU and hospital mortality will be determined per person-time at risk in each group (IEN vs CEN) with associated 95% CI. Significant differences between groups will again be determined by two sample t-test. Multivariate logistic regression will evaluate associations between baseline characteristics and the type of EN chosen.

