### Strengths and limitations

This is a pragmatic study with broad inclusion criteria that should be generalizable to most critically ill patients. It uses the newly implemented EMR at all institutions in Hamilton to generate a large amount of patient data without manual review. It examines two understudied areas of critical care medicine, the effects of EN strategy on diarrhea and the effect of NIPPV on nutrition.

The main weakness in our study is the retrospective strategy. It may be challenging to understand whether differences in diarrhea and daily caloric intake are due to covariates and the severity of illness or the EN strategy chosen. Furthermore, our study centres are all located in Hamilton, Canada; meaning that our findings may be less generalizable to other centres with different practice patterns.

The ENND-GOALs study will generate relevant, pragmatic data regarding EN strategy and diarrhea in the critically ill. Moreover, it will support the findings and inform posthoc analysis from the upcoming INVENTS-ICU RCT, which will also evaluate the differences between IEN and CEN.

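### The Table 1 outcome regressions carry NIPPV as their only respiratory-support covariate and omit Day 1 invasive ventilation and renal replacement therapy, although both are collected

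*Protocol article*

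**What the plan says.** Table 1 (Statistical Plan) has three rows that use logistic regression.

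- Diarrhea, and mortality with length of stay, share one list: "Age, sex, type of nutrition (IEN/CEN), antibiotics, GI comorbidities, vasopressor/inotropes, daily caloric intake, NIPPV, surgical/trauma/medical admission".
- The caloric-requirement row gives the same terms in another order: "NIPPV, Age, sex, antibiotics, GI comorbidities, type of nutrition (IEN/CEN) vasopressor/inotropes, daily caloric intake, surgical/trauma/medical admission".

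The Data collection section records more than this. Its Day 1 clinical data include "ventilation status, inotrope/ vasopressor use, renal replacement therapy", and ventilation mode is also recorded daily. It gives the purpose of the baseline data: "baseline characteristics will be recorded to determine factors associated with intolerance of IEN or CEN and with the development of ICU-acquired diarrhea".

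Data analysis says that, for secondary outcomes, patients will also be "divided into those who have received NIPPV and those who have not". It also plans a separate logistic model relating baseline characteristics to the type of enteral nutrition chosen.

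Two passages bear on confounding. The Introduction reports that one nutrition society "recommends avoidance of IEN in high-risk patients". Strengths and limitations concedes that it may be hard to tell whether differences in diarrhea and caloric intake are "due to covariates and the severity of illness or the EN strategy chosen".

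**The concern.** Feeding mode was chosen at the bedside, so the regressions are the only place where the plan adjusts the IEN/CEN contrast for how sick patients were. Table 1 contains no severity score. Its acuity-related terms are vasopressor/inotropes, admission type and NIPPV. Two organ-support measures that are collected to study diarrhea and feeding intolerance enter none of the outcome models.

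Under Participants, an enteral nutrition prescription is enough for entry, so intubated patients and patients on no support can both be in the cohort. With a yes/no NIPPV term these two kinds of patient form one reference category. If the intubated share differs between IEN and CEN, and intubation is related to the outcome beyond what the other covariates capture, the difference is carried by the IEN/CEN odds ratio. The NIPPV coefficient, which is also of interest to the study, would then be a contrast against a mixed group whose composition is not described.

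**Working it through.** **Step 1. Compare the lists.**

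| Measure | Collected | Diarrhea model | Caloric model | Mortality/LOS model |
|---|---|---|---|---|
| NIPPV | yes | yes | yes | yes |
| Vasopressor/inotropes | Day 1 and daily | yes | yes | yes |
| Admission type | yes | yes | yes | yes |
| Invasive ventilation | Day 1 and daily | no | no | no |
| Renal replacement therapy | Day 1 | no | no | no |

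The omission is the same in all three rows.

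**Step 2. The plan's own scale for the effect.** Sample size uses 25.1% (IEN) and 17.5% (CEN), two-sided alpha 0.05 and power 0.80. With pooled variance, mean proportion 0.213:

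n = [1.96·√(2·0.213·0.787) + 0.842·√(0.251·0.749 + 0.175·0.825)]² / 0.076² ≈ 455 per group.

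This reproduces the stated figure, which does not depend on the present point. The planning odds ratio is (0.251/0.749)/(0.175/0.825) = 1.58.

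**Step 3. Illustration for diarrhea.** The document gives no ventilation prevalence by feeding group, so every input here is an assumption: no true IEN effect, 12% diarrhea in non-intubated patients (odds 0.12/0.88 = 0.136), and no other covariates. With odds ratio V for invasive ventilation, the risk in intubated patients is r = 0.136V/(1 + 0.136V). The risk in a group with intubated share s is s·r + (1 − s)·0.12.

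| V | Intubated, IEN vs CEN | Diarrhea, IEN vs CEN | Apparent OR |
|---|---|---|---|
| 1.5 | 40% vs 60% | 14.0% vs 15.0% | 0.92 |
| 1.5 | 30% vs 70% | 13.5% vs 15.5% | 0.85 |
| 1.5 | 50% vs 80% | 14.5% vs 16.0% | 0.89 |
| 2 | 40% vs 60% | 15.8% vs 17.7% | 0.87 |
| 2 | 30% vs 70% | 14.8% vs 18.6% | 0.76 |
| 2 | 50% vs 80% | 16.7% vs 19.5% | 0.83 |
| 3 | 40% vs 60% | 18.8% vs 22.2% | 0.81 |
| 3 | 30% vs 70% | 17.1% vs 23.9% | 0.66 |
| 3 | 50% vs 80% | 20.5% vs 25.6% | 0.75 |

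With equal shares, or with V = 1, the apparent odds ratio is 1.00. If the shares are swapped so that IEN patients are intubated more often, the values invert, to between about 1.1 (1/0.92) and 1.5 (1/0.66).

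**Step 4. Illustration for mortality.** Assume 25% mortality if ventilated and 10% if not (odds ratio 3), again with no true effect and no other covariates.

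- Ventilated 70% of CEN, 40% of IEN: CEN 0.7·0.25 + 0.3·0.10 = 20.5%; IEN 0.4·0.25 + 0.6·0.10 = 16.0%; OR = (0.160/0.840)/(0.205/0.795) = 0.74.
- Ventilated 70% of CEN, 55% of IEN: IEN 18.25%; OR = 0.87.

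Both steps are crude contrasts. They show what an unadjusted imbalance could do, not the bias left in the planned models.

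**The case against.** **The variables are not ignored.** Ventilation status and renal replacement therapy are baseline characteristics, and Data analysis relates baseline characteristics to the type of enteral nutrition chosen. A reader might infer that they are collected and never used; that is wrong. But the feeding-choice model is not said to feed the outcome models, for example as a propensity score. The wider reference to baseline characteristics for the caloric model points back to Table 1, which omits both. This part of the objection narrows the point to the outcome regressions and does not remove it.

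**Severity may not drive feeding mode.** The Discussion says that institutional practice and practitioner comfort often dictate the method. The Introduction does not define high-risk patients or equate them with intubated patients. Strengths and limitations calls the retrospective strategy the main weakness; it does not name severity as the main confounder, and it speaks of diarrhea and caloric intake, not mortality. All of this stands, so bias is a possibility and not an established fact.

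**Coding is inferred.** Table 1 does not say how NIPPV enters the models; the received/not-received split is stated for secondary-outcome grouping. Coding may be left to a fuller plan. That stands, and the mixed reference group is therefore conditional. The absence of invasive ventilation and renal replacement therapy from named covariate lists is not conditional.

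**The primary result is untouched.** It is a descriptive proportion with a confidence interval, with covariates marked as not applicable. This stands.

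**Conclusion.** The point holds in a limited form. All three Table 1 outcome regressions name their covariates, NIPPV is the only respiratory-support term, and invasive ventilation and renal replacement therapy are absent although both are collected on Day 1. Because Table 1 is headed as the statistical plan and lists each term, this is a stated choice and not a detail left open.

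If NIPPV is coded as in the Data analysis split, part of any severity-driven choice of feeding mode can remain in the adjusted IEN/CEN odds ratios. The apparent odds ratios of 0.66 to 0.92 for diarrhea and 0.74 to 0.87 for mortality rest wholly on assumed prevalences and effects without other adjustment. Vasopressor and admission-type terms would remove some of it.

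Two stronger readings are not supported. A reader might infer that IEN will look protective, but without ventilation prevalence by group the direction is unknown and can reverse. A reader might also infer that the NIPPV coefficient cannot be interpreted; NIPPV against no NIPPV is a definable, though heterogeneous, contrast.

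The change is worth making because it uses data already collected and addresses a weakness that the article itself concedes.

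**What to change.** In each of the three Table 1 regressions:

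1. Keep the NIPPV term and add Day 1 invasive ventilation, so that invasive support, NIPPV and no support are distinguished. Do not replace NIPPV by Day 1 status alone: Participants admits patients whose 48 hours of NIPPV fall at any time, and the study wants to describe them.
2. Add Day 1 renal replacement therapy.
3. State that the vasopressor/inotrope covariate is the Day 1 value.

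Admission albumin is optional; nothing in the document ties it to feeding choice.

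**Cost.** No new data, a wording change to Table 1, and about two more parameters. The loss of precision should be small and would be felt most in the mortality model. As an assumption, if mortality were in the 7.4% to 13.9% range that the Introduction quotes from an earlier trial, about 500 patients would give 37 (0.074 × 500) to 70 (0.139 × 500) deaths. Counting one parameter per listed term and two for the three-level admission type, the current list has 10 and the amended list 12. Deaths per parameter would fall from 3.7–7.0 to 3.1–5.8, so the mortality model is thin either way. The Timeline places completion of analysis in December 2025, after extraction, so the amended list can be recorded before analysis starts.

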## Discussion

EN has become the standard of care for nutritional support in most critically ill patients. Despite this, nutrition and the consequences of delivering it are discussed by multidisciplinary teams and often family members daily in the ICU. Abdominal pain, distention, vomiting, and diarrhea are frequent [11], and there is little to no high-quality evidence outlining which EN strategies best mitigate these risks. Institutional practices and practitioners’ comfort with specific strategies often dictate the EN method.

Diarrhea is a frequent problem amongst critically ill patients that is also understudied. It has been shown in a recent multicentre prospective study to affect greater than 38% of critically ill patients [12]. Moreover, diarrhea is particularly distressing to patients and their families and has been shown in several studies to be associated with increased length of stay. Selecting an EN strategy that would be less likely to result in diarrhea would be valuable to clinicians and patients alike.

Physiological studies have suggested the potential benefits of IEN over CEN [20]. This is despite CEN being more common than IEN in most critical care units [20]. In healthy volunteers, IEN causes more rapid gastric emptying, increased superior mesenteric arterial flow, and physiologic insulin peaks compared to CEN [20]. While caution should be used when generalizing these findings to critically ill patients, a small RCT of 120 patients did find that mechanically ventilated patients on IEN were more likely to meet caloric targets. Furthermore, interrupted feeds for procedures and loss of enteral access are more likely to affect the daily caloric intake amongst patients on CEN. With malnutrition still being a large problem in Canadian ICU, IEN may be a potential solution and led us to evaluate the effects of EN strategy on the daily caloric intake and PN [21]

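### Admitting hospital is recorded at baseline, but neither it nor calendar period is in any Table 1 outcome regression, so site or period differences may be read as an IEN/CEN effect

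*Protocol article*

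**What the plan says.** **Collection.** Under Data collection, the baseline characteristics include "renal replacement therapy), admitting hospital, medical comorbidities (prior GI disease, previous luminal surgeries". The same section says that they are recorded to find factors associated with feeding intolerance and with ICU-acquired diarrhea.

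**Models.** Table 1 has three rows with logistic regression.
- Diarrhea: "Age, sex, type of nutrition (IEN/CEN), antibiotics, GI comorbidities, vasopressor/inotropes, daily caloric intake, NIPPV, surgical/trauma/medical admission".
- Caloric intake and parenteral nutrition: "NIPPV, Age, sex, antibiotics, GI comorbidities, type of nutrition (IEN/CEN) vasopressor/inotropes, daily caloric intake, surgical/trauma/medical admission".
- Mortality and length of stay: the same items as the diarrhea row.

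Hospital and calendar period are in none of them. Nothing in the article describes stratification, a random effect or clustering by site.

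**Primary comparison.** The diarrhea incidence row has no covariates and plans "Descriptive statistics (proportion of patients with diarrhea) and corresponding 95% CI" only.

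**Exposure.** The Discussion states: "Institutional practices and practitioners’ comfort with specific strategies often dictate the EN method".

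**Calendar windows (Participants).** For SJHH, "this is between January 1, 2018, and December 31, 2023". For the two HHS sites, "this is between June 4, 2022, and December 31, 2023".

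**The concern.** A variable confounds the IEN/CEN comparison if it is related to both feeding mode and outcome and is not adjusted for. On the article's own account, institution is a plausible influence on feeding mode. A link to outcome is also plausible: diarrhea is read from nursing flowsheets, aspiration is whatever the ICU team documents, and the sites cover different years. The listed covariates describe the patient and the treatment. None describes local charting or calendar time.

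The adjusted OR is the only planned IEN/CEN estimate for diarrhea with any control of confounding. If hospital matters and is left out, that OR carries a bias that data already held could reduce, and so do the adjusted results for calories/parenteral nutrition and mortality/length of stay. Table 1 is headed as the statistical plan and lists its covariates item by item, so this is a stated choice and not a detail left for later.

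**Working it through.** **1. Planning effect, used as the yardstick.** Sample size section: 25.1% IEN, 17.5% CEN, two-sided alpha 0.05, power 0.80.
- Difference: 25.1 − 17.5 = 7.6 points. OR = (0.251/0.749)/(0.175/0.825) = 1.58.
- n per group = [1.960·√(2·0.213·0.787) + 0.842·√(0.251·0.749 + 0.175·0.825)]² / 0.076² = 454.4, rounded up to 455. The stated figure reproduces.

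**2. Calendar overlap.**
- SJHH: 6 × 365 + 1 = 2191 days.
- HHS: 211 days in 2022 + 365 in 2023 = 576 days.
- Share of the SJHH window without an HHS counterpart: (2191 − 576)/2191 = 74%.

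Site and period are thus entangled, but not completely, because SJHH also contributes to the common window.

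**3. Possible size of site confounding.** The documents give no site-level IEN use or diarrhea rates, so every input here is an assumption: two hospital groups of equal size, no true effect of feeding mode, and no help from the listed covariates. With IEN share s and diarrhea risk r in each group:

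P(D|IEN) = Σ s·r / Σ s; P(D|CEN) = Σ (1−s)·r / Σ (1−s).

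| IEN share | Diarrhea | P(D\|IEN) | P(D\|CEN) | Crude OR |
|---|---|---|---|---|
| 30% vs 30% | 30% vs 15% | 22.5% | 22.5% | 1.00 |
| 50% vs 10% | 20% vs 20% | 20.0% | 20.0% | 1.00 |
| 30% vs 20% | 25% vs 17.5% | 22.0% | 21.0% | 1.06 |
| 40% vs 10% | 30% vs 17.5% | 27.5% | 22.5% | 1.31 |
| 50% vs 10% | 30% vs 15% | 27.5% | 20.4% | 1.48 |

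Fourth row in full: (0.4·0.30 + 0.1·0.175)/0.5 = 0.275; (0.6·0.30 + 0.9·0.175)/1.5 = 0.225; OR = (0.275/0.725)/(0.225/0.775) = 1.31. The spurious 5.0 points are about two thirds of the 7.6-point planning difference.

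In the last row the spurious difference is 7.1 points. With 500 patients (150 IEN, 350 CEN), a two-sided 5% test of the crude proportions would reject with probability 42%; with 1000 patients, 69%.

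The bias can also go the other way. If the 40%-IEN group has the lower diarrhea risk (17.5% vs 30%), then (0.4·0.175 + 0.1·0.30)/0.5 = 0.20, (0.6·0.175 + 0.9·0.30)/1.5 = 0.25, and OR = (0.20/0.80)/(0.25/0.75) = 0.75.

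Within each hospital group the OR is 1.00 in every example, by construction.

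**The case against.** **Hospital is not absent from the whole plan.** A reader might infer that no model uses it. Data analysis also plans a regression of the type of EN chosen on baseline characteristics, and these include hospital. Its text on the caloric-target regression also speaks of baseline characteristics, although it refers back to Table 1. This stands, so the point is limited to the Table 1 outcome regressions. The model of EN choice adjusts no outcome comparison and does not remove the problem.

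**Confounding by site is possible, not shown.** A reader might infer that site differences will appear as a feeding effect. The Discussion sentence is general background, says only that this is often so, and also names practitioner comfort. No site-level case mix, charting practice, IEN share or diarrhea rate is given. All sites chart in the same record system, and samples from both institutions are adjudicated by two reviewers. Bias arises only if both feeding mode and outcome still differ by site after the listed covariates, and admission type, antibiotics and vasopressors may absorb part of it. This stands too, and it is why the range includes 1.00.

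**The primary outcome is not an OR.** It is an unadjusted proportion per group, so adding terms to the regressions leaves it as it is. This is correct; the crude proportions need an adjusted estimate beside them.

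**Confounding is acknowledged.** Strengths and limitations names covariates and severity of illness. It does not name site or period as confounders.

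**Other covariates.** It is tempting to ask also for Day 1 renal replacement therapy, or for Day 1 ventilation status in place of NIPPV. The first is a covariate preference. The second would lose NIPPV received later in the stay, which is a stated interest of the study.

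**Conclusion.** The point holds for the diarrhea, caloric/parenteral nutrition and mortality/length-of-stay regressions in Table 1. Hospital is recorded partly to explain diarrhea and then left out of the diarrhea model. Calendar period is left out as well, although 74% of one hospital's window has no counterpart at the other two sites. The unadjusted primary proportions are equally exposed.

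In these examples, with no true effect, the crude OR runs from 1.00 to about 1.5, against a planning OR of 1.58, and can fall below 1 if the site pattern is reversed. These are illustrations of the crude comparison under assumed rates and equal group sizes, with nothing absorbed by the listed covariates. They do not estimate the bias in the adjusted ORs, whose size the documents do not allow one to determine. The case for the change rests on a plausible confounder that is already measured and costs little to include.

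**What to change.** 1. Add admitting hospital (three-level fixed effect) and calendar period (for example before versus from June 4, 2022) to each Table 1 outcome regression. Keep the NIPPV term.
2. Present the hospital-adjusted IEN/CEN OR for diarrhea, with its 95% CI, beside the crude proportions.
3. Repeat the diarrhea model in the common window, June 4, 2022 to December 31, 2023, as a sensitivity analysis.

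**Cost.** Two parameters for hospital and one for a two-level period, so three per model. Hospital is already on the collection list, and the ethics section says that the hospitals have provided admission dates. The period term is estimable because SJHH contributes patients on both sides of the cut. Precision falls if a hospital uses almost only one feeding mode, but readers would need to know of that lack of overlap anyway. The common-window analysis drops the earlier SJHH patients and will be less precise.
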